### Trial design

IMOP is a double blind, randomised, placebo controlled trial in a single clinical setting. Active and placebo treatment will be allocated in a 1:1 ratio. The primary outcome measures are the effect of outpatient pre-induction cervical ripening with IMN on:

i. The elapsed time from hospital admission to delivery (defined as the time from admission to inpatient induction or admission in labour to delivery – either vaginally or by caeserean section)

ii. The costs of induction of labour

iii. Women's experience of induction of labour (maternal satisfaction)

iv. Operative delivery rates

### Setting

The study will be carried out in a large UK NHS teaching hospital (Princess Royal Maternity, Glasgow).

### Participants

#### Inclusion criteria

Women scheduled for induction of labour will be invited to participate in the study. The rationale for induction of labour in the majority (but not all) of these women will be post-dates pregnancy. The hospital protocol is to offer induction of labour after 40 weeks and 10 days gestation, and in the PRIM study, "post dates" was the principal reason for induction of labour in over 70% of subjects. The other inclusion criteria will be as follows:

▪ Bishop Score ≤ 6

▪ Singleton pregnancy

▪ Nulliparity

▪ ≥37 completed weeks of gestation

▪ Willing to self administer vaginal tablets

#### Exclusion criteria

▪ fetal compromise of sufficient severity that daily fetal monitoring is scheduled.

### Recruitment and consent

Subjects will not be formally recruited to the study until the decision to induce labour is made. Potential subjects will be informed about the trial and given written information in the third trimester. Those women who wish to participate and who understand the nature of the trial will be asked to complete and sign two copies of the consent form. Those women who do not wish to participate, or who are ineligible will be asked (verbally) for permission to record some basic data so that the generalisability of the trial can be subsequently assessed.

Women scheduled for induction of labour at term will be recruited and randomised at an antenatal visit by the clinical research fellow, up to seven days prior to scheduled admission for induction of labour. A vaginal examination will not be repeated if one has been done and each of the components of the Bishop score documented within 7 days of anticipated start of outpatient treatment. Women willing to participate in the study will be given their randomised study medication (either IMN tablets or placebo) at this visit, with instructions to self-administer the tablets vaginally starting 48 hours prior to the scheduled time of admission for induction of labour.

### Randomisation

Randomisation to IMN or placebo will be in the ratio 1:1, using randomised permuted blocks. The randomisation schedule will be generated by the Study Data Centre at the Centre for Healthcare Randomised Trials (CHaRT) at Aberdeen University. The randomisation schedule will be used by the Clinical Trials section of the pharmacy at the Western Infirmary, Glasgow, to make up treatment packs (either active or placebo) for each patient, each labelled with the relevant unique study number. Active and placebo treatments will otherwise appear identical, so that this will be a double blind study. A copy of the randomisation schedule will be held at the Clinical Trials Pharmacy at the Western Infirmary, and at CHaRT only. None of the investigators will have access to the schedule until completion of the study.

Within one hour after recruitment of each subject, the pack number for the subject will be allocated by phone call to the automated telephone randomisation service located at CHaRT in Aberdeen.

### Cessation of randomised treatment

The following will be indications for early cessation of treatment

• Admission in labour

• Fetal membrane rupture

• Bleeding

The general practitioner and referring obstetrician will be informed. The clinical research fellow will still collect outcome data from women who have stopped taking their study medication, unless the participant asks that her data are not collected. Women who are admitted in labour, women who experience spontaneous membrane rupture and those who experience antepartum haemorrhage will be asked not to take any more doses of study drug, but will still be followed up. Women in whom fetal membranes rupture after taking study medication will be asked to come into the hospital for assessment. They will normally be offered the option of immediate augmentation with syntocinon, or delaying augmentation with syntocinon until the next morning, depending on their preference.

In the event of a participant deciding to stop their medication themselves, or if cessation is recommended by the supervising obstetrician, the clinical research fellow will complete the withdrawal CRF. The clinical research fellow will also inform the hospital pharmacy, and return any unused medication. The general practitioner and referring obstetrician will be informed.

### Interventions

The intervention is one tablet inserted vaginally on three occasions every 16 hours. In the experimental (IMN) group, a 40 mg IMN tablet will be self-administered vaginally by the patient at home 48, 32 and 16 hours before scheduled admission for induction of labour. In the control group, a placebo tablet, with an identical appearance to that of IMN, will be self-administered vaginally by the patient at home 48, 32 and 16 hours before scheduled admission for induction of labour.

#### Rationale for dosage

IMN will be given in a dose of 40 mg. Previous studies have shown that this dose is effective in inducing cervical ripening both in the first trimester [8,9] and at term [11] (PRIM) with no clinically significant effects on maternal haemodynamics [10] and without unacceptable side effects (PRIM) [11].

#### Rationale for dosage intervals

We have opted for a 16 hour dosage interval. Our previous studies suggest that systemic absorption of IMN from vaginally administered tablets is slow [31], thus a short dosage interval might lead to accumulating serum levels of drug. In the PRIM study, we gave a repeated dose of IMN after 16 hours. Haemodynamic and symptomatic side effects after the second dose of IMN were, if anything, less than after the first, suggesting that a 16 hour treatment interval is not associated with unacceptable systemic levels of drug.

#### Rationale for duration of treatment

We have opted to give IMN for 48 hours prior to admission. We anticipate that the ripening effects of IMN will continue after the first 24 hours, so that the cervix might be fully ripened by 48 hours after treatment.

With the exception of trial medication, subjects will normally be managed according to the induction of labour protocol. Thus, once a subject is admitted after trial medication, she will be managed according to the normal protocol, ignoring the use of the trial medication.

### Outcomes

Data on the primary and secondary outcomes listed below will be recorded.

#### Primary

i. Elapsed time interval from hospital admission to delivery (defined as the time from admission for inpatient induction or admission in labour to delivery – either vaginally or by caesarean section)

ii. Costs to the health service of induction of labour

iii. Women's experience of induction of labour

#### Secondary

iv. Primary clinical outcome (elapsed time from admission to delivery) for the subgroup of women who deliver vaginally

v. Operative delivery rates

vi. Incidence of unscheduled admission for reasons other than labour commencing

vii. Duration and frequency of neonatal admissions to special care

viii. Incidence of adverse maternal and fetal outcomes such as uterine hypercontractility, postpartum haemorrhage (maternal outcomes) and meconium stained liquor, five minute Apgar of less than seven (fetal outcomes)

ix. Length of labour

x. Oxytocin augmentation rates

xi. Epidural usage

xii. Proportion with unfavourable cervix at 24 hours after admission

xiii. Requirement for additional inpatient cervical ripening agent

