**Methods/design:**

The aim of this study is to determine whether IMN self administered by women on an outpatient basis improves the process of induction of labour. Specifically, we hypothesise that the use of outpatient IMN will result in a shorter inpatient stay before delivery, decreased costs to the health service and greater maternal satisfaction with ripening and induction of labour, compared with placebo treatment.

In the study described here (the "IMOP" study), women scheduled for induction of labour at term, and who require pre-induction cervical ripening will be randomised to self-administer at home either IMN 40 mg, or a placebo, each vaginally, at 48 hours, 32 hours and 16 hours before scheduled hospital admission.

After admission to hospital, treatment will revert to the usual induction of labour protocol. We will compare the primary outcomes of the elapsed time interval from hospital admission to vaginal delivery, the costs to the health service of induction of labour, and women's experience of induction of labour in the two groups.

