## Methods and trial design

### Aims of the trial

The aim of this trial is to test the hypothesis that IMN, 40 mg every 16 hours to a total of three doses improves the process of induction of labour. Specifically we aim to test the hypotheses that outpatient pre-induction cervical ripening with IMN:

i. Reduces the elapsed time from hospital admission to delivery

ii. Reduces the costs of induction of labour

iii. Improves women's experience of induction of labour

iv. Does not increase operative delivery rates

Women scheduled for induction of labour at term, and who require pre-induction cervical ripening will be invited to participate in the study. Participants will be randomised into an active (IMN) or a control (placebo) group and asked to self-administer either IMN 40 mg, or a placebo, each vaginally, at 48 hours, 32 hours and 16 hours before scheduled admission. After admission to hospital, treatment will revert to the usual induction of labour protocol whereby prostaglandins are given until cervical ripening is achieved, and fetal membrane rupture is performed thereafter, followed by syntocinon if contractions do not start spontaneously. Data on the outcome measures listed below will be collected and compared in the two groups.

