### Statistical issues

#### Sample size calculation

Three hundred women will be recruited, of whom about 150 will be in the experimental and about 150 will be in the control (placebo) group. The primary outcome on which this study is powered is the time interval from hospital admission to delivery. In women undergoing induction of labour with Bishop scores 0–4 and 5–8, the mean (SD) induction to delivery intervals are 19.65 (10.75) hours and 15.17 (6.80) hours respectively ([name], data on file). With 150 women in each of the IMN and placebo groups (300 in total) the study has 96% power at a 5% level of significance to detect a difference in mean time from admission to delivery of 4 hours, assuming a common standard deviation of 9 hours, using a two sample two sided t-test.

Women's experience of induction of labour will be explored qualitatively and quantitatively. As in the PRIM study, we will ask women to indicate satisfaction with the ripening process on a visual analogue scale. Assuming similar results in the PRIM study (that those pretreated with IMN will give a mean (SD) score of satisfaction of 7.0 and those who have prostaglandins only as the active ripening agent will give a mean (SD) score of satisfaction of 5.8, with a common standard deviation of 3.0, the study has 93% power to detect a significant difference in satisfaction rates, given a sample size of 150 in each group. Statistical power of 90% or above (at the 5% significance level) is maintained if the number of evaluable patients in each group is 133 or greater.

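### The abstract ends the primary interval at vaginal delivery while the body ends it at delivery by any route, and secondary outcome iv compares times in a subgroup formed after randomisation

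*Protocol article*

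**What the plan says.** **Primary interval.** The abstract (Methods/design) names "the primary outcomes of the elapsed time interval from hospital admission to vaginal delivery". The Outcomes section (Primary, item i) runs it from "admission for inpatient induction or admission in labour to delivery – either vaginally or by caesarean section", and Trial design has nearly the same wording: "admission to inpatient induction or admission in labour to delivery – either vaginally or by caeserean section". The Sample size calculation does not restrict mode: "The primary outcome on which this study is powered is the time interval from hospital admission to delivery". Statistical analysis ground rules also refers only to admission and delivery, plans a two-sample t-test followed by a linear model, and puts all primary analyses on an intention-to-treat footing.

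**Vaginal deliveries only.** Outcomes (Secondary, item iv) adds the "Primary clinical outcome (elapsed time from admission to delivery) for the subgroup of women who deliver vaginally". For secondary outcomes the ground rules plan t-tests, Wilcoxon tests or chi-squared tests, with covariate adjustment.

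**Mode of delivery as an outcome.** Aims of the trial includes the hypothesis that IMN "Does not increase operative delivery rates". Trial design lists operative delivery as primary and Outcomes lists it as secondary. The Data Monitoring Committee section gives the caesarean rate as an example of what the interim analysis will cover.

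**The concern.** There are two separate problems.

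First, the endpoint on which the trial is powered has two definitions in current text. They are different quantities. Under the abstract's version a woman delivered by caesarean has no value for a t-test, and leaving her out would break the intention-to-treat rule and shrink the sample. Two published definitions also leave room to choose between them once results are known.

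Second, outcome iv selects on mode of delivery. Mode is decided after treatment starts, and the trial itself treats it as something IMN might change. If caesarean is more likely in women whose labour would have been long, a change in the caesarean rate changes which women remain in the vaginal group. The arms compared there are then no longer the randomised ones. In particular, a treatment that avoided caesareans could look slower, because women with long labours would join its vaginal group.

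**Working it through.** **1. The definitions side by side**

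| Place | End of interval |
|---|---|
| Abstract, Methods/design | vaginal delivery |
| Aims of the trial, hypothesis i | delivery |
| Trial design, item i | vaginal or caesarean |
| Outcomes, Primary i | vaginal or caesarean |
| Sample size calculation | delivery, mode not restricted |
| Statistical analysis ground rules | delivery, mode not restricted |

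Only the abstract differs. Condensing does not explain this, because the abstract adds a restriction that the body lacks.

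**2. The stated power belongs to the any-delivery endpoint**

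Inputs from the Sample size calculation: 150 per arm, difference 4 h, SD 9 h, two-sided 5%.

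- Standard error = 9 × √(2/150) = 1.04 h.
- Power ≈ Φ(4/1.04 − 1.96) = 0.971; the exact noncentral t gives 0.970. The protocol states 96%, so the figure reproduces to about a point, with all 150 women per arm contributing.

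**3. Power if only vaginal deliveries counted**

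Same 4 h and SD 9 h, with equal caesarean rates in both arms. The rates are assumed, since the documents give none.

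| Caesarean rate | Women per arm | Power |
|---|---|---|
| 20% | 120 | 0.93 |
| 30% | 105 | 0.90 |
| 40% | 90 | 0.85 |
| 50% | 75 | 0.78 |

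**4. Selection bias in outcome iv**

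Simulation of 1,000,000 women with no true effect of IMN on the latent time to vaginal delivery.

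- From the protocol: mean 19.65 h (its figure for Bishop scores 0–4) and SD 9 h.
- Assumed: latent times normal with a floor of 1 h; caesarean more likely with longer latent time (logit slope 0.5 or 1.0 per SD); caesarean performed at 60–100% of the latent time; 30% caesarean on placebo.

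Differences are IMN minus placebo, in hours; the two values are for slopes 0.5 and 1.0.

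| IMN caesarean rate | Vaginal-only difference | Any-delivery difference |
|---|---|---|
| 20% | +0.40, +0.71 | +0.43, +0.46 |
| 25% | +0.21, +0.35 | +0.22, +0.23 |
| 30% | 0, 0 | 0, 0 |
| 35% | −0.20, −0.34 | −0.21, −0.22 |
| 40% | −0.42, −0.69 | −0.42, −0.43 |

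The vaginal-only shift is pure selection. The any-delivery shift is a real difference in time to delivery, produced by the use of caesarean.

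**5. A check by hand, with harsher assumptions**

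Suppose 70% of placebo women deliver vaginally at a mean of 17 h, and IMN turns a further 5% from caesarean into vaginal births at 28 h. The IMN vaginal-only mean is (0.70 × 17 + 0.05 × 28)/0.75 = 17.73 h. The shift is 0.05/0.75 × (28 − 17) = 0.73 h in the unfavourable direction, although caesareans were avoided.

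**6. Scale**

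0.4 to 0.7 h is 10% to 18% of the 4 h target. It is below one standard error of the difference: 1.04 h with 150 per arm, and 9 × √(2/105) = 1.24 h with 105 per arm.

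**The case against.** The best defence is that the body of the protocol is consistent and only the abstract departs from it. An analysis by the abstract's wording would have to override every other section, and a statistical analysis plan is to be signed before the codes are broken. That makes a wrong analysis unlikely, but it does not make the abstract right.

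A reader might go further and infer that neither definition copes with caesarean. The documents do not support that. Any-delivery time has a value for every woman who is admitted and delivers, respects intention to treat, and measures what the trial sets out to shorten, namely the stay before delivery. An early caesarean does count as a short time, but that is a matter of interpretation. The protocol addresses it by reporting operative delivery, letting the monitoring committee see the caesarean rate, and including surgical procedures in the costs.

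A reader might also take outcome iv to be the protocol's chosen safeguard against short times due to caesarean, or expect the two means to move in opposite directions. No section gives outcome iv that role. In the simulation both means move the same way, rising when IMN lowers the caesarean rate and falling when it raises it.

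It is also fair to say that outcome iv is one of ten secondary outcomes, that its bias cannot reach the powered analysis, that every magnitude here is assumed, and that labelling it descriptive would be enough to prevent a misleading test. All of this stands. What remains is that the protocol plans formal tests for its secondary outcomes, and covariate adjustment does not by itself restore the randomised comparison.

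**Conclusion.** The contradiction over the primary interval is certain from the text and must be reconciled, because it concerns the powered endpoint. The any-delivery definition is the one that the power calculation, the planned t-test and the intention-to-treat rule fit.

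The weakness of outcome iv is real but lesser. It arises only if IMN changes the caesarean rate or who is delivered by caesarean. For a 10-point difference in either direction from an assumed 30%, it comes to roughly 0.4 to 0.7 h. The documents contain no caesarean rate or timing from which to fix the true size. None of the protocol's stated power figures is shown to be wrong, and the primary analysis as defined in the body is not undermined.

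**What to change.** 1. In the abstract, define the primary interval as the body does, ending at delivery "either vaginally or by caesarean section". State that the result will be read alongside operative delivery rates, and give that outcome one rank, since Trial design and Outcomes now differ.
2. Replace outcome iv with time from admission to vaginal delivery in all randomised women, treating caesarean as a competing event. Report the cumulative incidence of vaginal delivery by arm with Gray's test. An equivalent choice is to place caesareans beyond the longest observed time and use a rank test.
3. Keep the vaginal-only means as description, without a test.

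Item 1 is wording only. Items 2 and 3 cost one extra standard analysis. The clinical case report form already covers the data needed, and the change can be fixed in the statistical analysis plan before the codes are broken.

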## Collection of outcome data

### Clinical data

Outcomes i, and iv – xiii will be recorded by the attending midwifery staff and the clinical research fellow onto a dedicated Case Report Form which will be placed in the case notes of each participating subject. Data will be collected on the health service resources used in the treatment of each woman and infant during the period between randomisation and hospital discharge to determine outcome ii. The trial data collection forms will record the duration and intensity of maternal and neonatal care, based on standard criteria for level of care, as well as profile maternal and neonatal complications. The start of labour will be defined as the start of regular uterine contractions 3 in 10 (mild to moderate in intensity), with a cervical dilation equal to or greater than 3 cm. Compliance will be assessed, as far as possible, by asking subjects to complete a diary card indicating when they took study medication.

### Collection of health cost data

Observational research will also be required at the Princess Royal Maternity Hospital, to provide details of the resources and staff inputs required for the induction of labour, as well as staff time, tests, procedures, drugs and equipment entailed by complications. Tick charts will be completed by health professionals caring for all women and infants in the trial, to document the key resource and staff inputs not recorded by the trial data collection forms. A similar approach to documenting health service resource inputs has successfully been applied to other National Perinatal Epidemiology Unit economic evaluations conducted alongside clinical trials [32].

Unit costs for each resource item will be calculated by sending the finance department at the Princess Royal Maternity Hospital a detailed questionnaire requesting cost data for the main resource categories of drugs, disposables, consumables, surgical procedures, equipment, staff and overheads, and then apportioning these to different categories of patient using a 'top-down' methodology. The finance department will be visited on several occasions in order to validate the cost data provided. If required, additional cost data will be collected from secondary sources. These will be obtained towards the end of the trial period to ensure that the costs are as current as possible for the final analysis.

### Collection of maternal satisfaction/acceptability data

Outcome iii, women's experience of induction of labour, will be drawn from two approaches. First, all women will be asked to complete a short questionnaire one hour before taking IMN using simple visual analogue scales for pain and anxiety. Baseline anxiety status will be assessed using the Eysenck anxiety scale. Women will be asked to note other symptoms and comments. We will ask women to complete further questionnaires after each 16 hour treatment period. Women will be given a stamped addressed envelope to send the completed forms to the social science researcher after delivery. All women will also be asked to complete a short follow-up questionnaire after delivery to ascertain satisfaction with cervical ripening, labour and delivery, pain scores and comments on the labour (e.g. duration). Women will be given the post delivery questionnaire at the hospital for completion, and asked to hand it in prior to discharge from hospital. In addition to the questionnaire strategies described above, a consecutive series of women recruited in the second year of the study will be approached for consent to being interviewed three weeks after delivery. We aim to interview 20 women in total. The interview will collect in-depth responses to the situation of women being at home during cervical ripening, including views on whether they felt in control of the situation, how easy it was to administer the tablet, whether they managed to administer the tablet at the prescribed intervals and any other positive or negative feelings.

